## Methods/design

### Patient recruitment

Patients included in the study will be adults (male or female aged ≥18 years) with a benign or malignant tumor in the right colon that require an elective right colectomy with curative intent. Patients will have a life expectancy of at least 12 weeks, with an adequate performance status (Eastern Cooperative Oncology Group Scale score ≤ 2). All patients will have voluntarily signed and dated an Ethics Committee-approved informed consent form before inclusion, obtained by the investigator or designee. Patients will be excluded if they have cT4b tumors, metastatic disease, planned colonic surgery along with other major concomitant procedures (e.g. liver resections, other intestinal resections), or have inflammatory bowel disease (i.e. Crohn’s disease or ulcerative colitis). Patients who are pregnant or suspected to be pregnant, have a comorbid illness or condition that would preclude the use of surgery, are undergoing emergency procedures, or are unwilling to comply with all follow-up study requirements will also be excluded. All patients will be screened and recorded during enrolment to identify any selection bias, which can be higher in observational studies [6].

Eligible patients will be recruited from the approved participating centers according to the surgeons’ experience with each technique. It is calculated that at least 1200 patients (300 per cohort) should be enrolled in the study. The assumptions for the sample size were based on the incidence of surgical wound infection and Clavien-Dindo grade > IIIa complications. The sample size is based on attaining a success rate of 85% for the primary endpoint, with the lower 95% confidence limit being no greater than 5% from the estimated success rate. Assuming a 2-sided interval, a total of 245–317 patients will be required within each cohort. Accounting for a 10% loss to follow-up, a total of 1200 patients will be recruited so that the four parallel cohorts will have sufficient power to make multiple comparisons.

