### Statistical analysis

All analyses is detailed in a statistical analysis plan. Patients from each cohort will be analyzed separately on an intent-to-treat basis. Descriptive statistics will be provided for all discrete variables in the form of rates and proportions with 95% confidence intervals (CI). Continuous variables will be escribed by mean, standard deviation, median and range. Overall survival, disease-free survival, local recurrence rate and metastasis rate will be estimated using the method of Kaplan Meier. Exploratory comparisons of discrete variables will be performed using a Chi-squared test, using continuity correction or Fisher’s exact test. Continuous variables will be compared using a Student’s t-test, or a non-parametric equivalent (Wilcoxon). Survival statistics will be based on a stratified log-rank test. All tests will be two sided with a *p*-value of less than 0.05 considered to indicate statistical significance.

An interim analysis is planned after having recruited 300 patients, 75 patients at least per cohort, in order to evaluate whether a success rate around 85% is achieved for each cohort; a lower limit of 75% is not acceptable, for which reason the data from the treatment groups with a success rate < 75% will be excluded from further analysis. None a priori expectations of differences can be made based in current literature.

A propensity score will be constructed as the individual prediction (in logit scale) of a logistic regression model in which the outcome is modeled with different potential confounding factors. The propensity score will be added as a continuous variable to adjust the risk models. The Generalized Linear Model (GLM) approach allows for the construction of multilevel and mixed models, which will be useful for controlling the inter-hospital random variability.

Secondary end-points will be analysed according to their characteristics: GLM with identity link will be used for operative time, number of harvested lymph nodes and length of stay, GLM with logit link will be used for unplanned conversion, complete mesocolic excision and R0 resection and Cox regression will be used for middle-term oncologic results: overall survival, disease-free survival, local recurrence and metastasis.

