### Sample size calculation

The assumptions for the sample size of this study have been developed based on the incidence of Surgical Wound Infection, as well as the incidence of Clavien-Dindo grade > III complications as seen in the Introduction. The sample size is based on attaining a success rate of 85% for the primary endpoint, with the lower 95% confidence limit being no greater than 5% from the estimated success rate. Assuming a 2-sided interval, a total of 245–317 subjects will be required within each cohort. Accounting for a 10% loss to follow up, a total of 1200 subjects will be recruited for this study. Several interim analysis are planned through the study in order to build new power analysis and adjust sample size accordingly if needed.

The design of this study envisages four parallel cohorts for which the sample size has been developed for each cohort according to a precision around an expected success rate with enough subject and sufficient power to make multiple comparisons within the appropriate method. Any statistical inferences drawn based on pairwise comparisons will be undertaken in a posteriori statistical analysis using a propensity score to account for confounding covariates.

The primary endpoint for success is defined as a patient meeting the following criteria:
Surgical Wound Infection 5% lower in the ICA group.Grade IIIb-IV Clavien -Dindo complications at 30 days post op 5% lower in the ICA group.

According to the current literature the the following numbers represent Surgical Wound Infection and Severe Complications in intermediate volume centers:

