**Table Taba:** 

ICA		ECA
Surgical Wound Infection	_4–5%_^5,8,10^	_10–14%_^5,8,10^
Morbidity Dindo 3b-4	1.1–5%^5,8^	8–11%^5,8^

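### The protocol says the literature supports no expected difference, yet it tabulates clear ICA–ECA differences, and the common 85% success rate used for sizing and at the interim does not fit them

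*Protocol article*

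**What the plan says.** In the protocol article, the Statistical analysis section describes an interim analysis after 300 patients, at least 75 per cohort. It checks whether each cohort reaches about 85% success and excludes from further analysis the data of any group below 75%. That paragraph closes with "None a priori expectations of differences can be made based in current literature".

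The Sample size calculation section uses one rate for all four cohorts: "The sample size is based on attaining a success rate of 85% for the primary endpoint". The precision target is a lower 95% limit at most 5 points below the estimate. The resulting requirement is worded as "Assuming a 2-sided interval, a total of 245–317 subjects will be required within each cohort". An allowance of 10% for loss then leads to 1200 in total, and Patient recruitment adds that "at least 1200 patients (300 per cohort) should be enrolled in the study".

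The same Sample size calculation section then defines success as wound infection, and separately grade IIIb–IV complications, each being 5% lower in the ICA group. It introduces a table whose "numbers represent Surgical Wound Infection and Severe Complications in intermediate volume centers". The table gives wound infection of 4–5% for ICA and 10–14% for ECA and, in the row "Morbidity Dindo 3b-4", 1.1–5% for ICA and 8–11% for ECA.

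The Outcomes section scores a patient as an event if either component occurs. No composite rate, overlap of the components or interval method is given.

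**The concern.** Two statements about the same literature cannot both stand: one says it supports no expectation of a difference, the other reports a difference with non-overlapping ranges for both components. The planning rate is affected as well. If the table is right, 85% lies below every ICA rate and, unless many patients have both events, above every ECA rate.

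Two things depend on that rate. One is the stated 5-point precision, which is calculated at 85% although the variance is larger at lower success rates. The other is the interim review, which reads every cohort against 85% and removes those below 75%. An ECA cohort performing as the cited literature suggests could be removed for doing so, and the ICA–ECA comparison that the study exists to make would lose that cohort.

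**Working it through.** **Inputs.** Success 85%, distance to the lower limit 5 points, two-sided 95% interval, 245–317 per cohort, 10% loss, 1200 in total (Sample size calculation); 300 per cohort (Patient recruitment), so 300 × 0.90 = 270 evaluable; component rates (table); either-event scoring (Outcomes); 75 patients and the 75% limit (Statistical analysis). Overlap of the components is not given, so it is varied.

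**1. The plan's own figure.** At p = 0.85 and d = 0.05:
- Wald, n = 1.96² × 0.85 × 0.15 / 0.05² = 196.
- Wilson lower limit, [p + z²/2n − z√(p(1−p)/n + z²/4n²)] / (1 + z²/n): the distance reaches 5 points at n = 246.
- Clopper–Pearson lower limit: n = 254.

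Wilson reproduces the low end, 245, to within one patient. The high end, 317, does not follow from the stated inputs, which does not show that it is wrong.

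**2. Composite success implied by the table.** Events are a + b with no overlap, 1 − (1−a)(1−b) under independence, and max(a, b) with complete overlap.

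| | ICA success | ECA success |
|---|---|---|
| No overlap | 1 − (0.05+0.05) = 90.0% to 1 − (0.04+0.011) = 94.9% | 1 − (0.14+0.11) = 75.0% to 1 − (0.10+0.08) = 82.0% |
| Independence | 0.95×0.95 = 90.3% to 0.96×0.989 = 94.9% | 0.86×0.89 = 76.5% to 0.90×0.92 = 82.8% |
| Complete overlap | 95% to 96% | 86% to 90% |

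ICA is 90–96% throughout, so 85% never fits it. For ECA to have 15% events, the overlap must be 10 + 8 − 15 = 3 of 8 points at the low end of the ranges, and 14 + 11 − 15 = 10 of 11 points at the high end.

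**3. Precision with 270 evaluable** (points from estimate to lower limit).

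| Success | Wald | Wilson | Clopper–Pearson |
|---|---|---|---|
| 75% | 5.16 | 5.49 | 5.61 |
| 82% | 4.58 | 5.02 | 5.11 |
| 82.8% | 4.50 | 4.95 | 5.04 |
| 85% | 4.26 | 4.75 | 4.83 |
| 90% | 3.58 | 4.16 | 4.22 |
| 94.9% | 2.62 | 3.31 | 3.34 |

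Wald meets 5 points when p(1−p) ≤ 270 × 0.05² / 1.96² = 0.1757, that is from about 77.3% success upward. With Wilson, a 5-point distance needs 273 evaluable at 82% and 323 at 75%.

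**4. Interim rule.** With 75 patients, below 75% means at most 56 successes (56/75 = 74.7%). P(X ≤ 56), X ~ Binomial(75, p):

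| True success | Chance of exclusion |
|---|---|
| 75% | 52% |
| 78% | 28% |
| 80% | 16% |
| 82% | 7% |
| 82.8% | 5% |
| 85% | 1.3% |
| 86% | 0.7% |
| 90% | 0.01% |

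**5. Power per ICA–ECA cohort pair**, 270 v 270, two-sided 5%, normal approximation, no multiplicity adjustment. The smallest gap with no overlap (10% v 18% events) gives 77%; the smallest under independence (9.75% v 17.2%) gives 72%; the largest (5.1% v 25%) exceeds 99%.

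**The case against.** The case for leaving the text alone has real substance.

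- **The reason for the 85%.** A reader might infer that 85% was chosen because no difference was expected. The documents do not say so. The sentence closes the interim paragraph, and the sample-size section gives its own rationale: precision per cohort, with pairwise comparisons made afterwards using a propensity score.
- **What the table shows.** It gives component rates only. A reader might take 75–82% as the protocol's ECA success rate, but that assumes no patient has both events; with complete overlap it is 86–90%.
- **Precision.** A reader might conclude that the ECA cohorts miss the 5-point target. That depends on the true rate, the interval method and the loss to follow-up. The worst shortfall is 0.5 point (Wilson) or 0.6 (Clopper–Pearson). Wilson at 82% exceeds the target by 0.02 point, and at 82.8% meets it. The printed range also reaches far enough to cover most implied ECA rates: Wilson needs 317 at 76%.
- **Power.** A reader might set the table's power against the 33–42% obtained for a 5-point gap in the composite. The protocol states 5% for each component, not for the composite, so that contrast has no basis in the text. Pooling over approach (assumed 540 v 540) gives 97% at 10% v 18%.
- **Context.** The table describes intermediate-volume centres, whereas Study setting recruits high-volume ones, and interim sample-size adjustment is planned.

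All of this limits the size of the consequence. None of it removes the contradiction, brings 85% into the ICA range, or addresses the interim rule. The sample-size section itself relies on this table, and adjusting the sample size does not protect a cohort whose data have been excluded.

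**Conclusion.** The point holds as a contradiction and a mismatched planning rate. The contradiction needs no assumption: both sets of component ranges are disjoint, and the text states a reduction with ICA. The misfit of 85% to ICA holds under any overlap. The misfit to ECA holds with no overlap or independence, and disappears with substantial overlap.

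The precision consequence is minor and conditional: about 3.3–4.2 points for ICA and 5.0–5.5 for ECA (Wilson, 270 evaluable, no overlap), before any allowance for clustering. The interim consequence matters more: a 5–52% chance of exclusion for an ECA cohort at the rates implied with no overlap or independence, against 1.3% at 85%. This assumes 75 evaluable patients per cohort, the rule applied to the observed proportion, and literature rates that carry over to these centres.

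**What to change.** - In Statistical analysis, delete the sentence on a priori expectations or correct it to agree with the table.
- In Patient recruitment and Sample size calculation, replace the common 85% with separate ICA and ECA planning rates. State the assumed overlap of the components and the interval method, and note that the table describes intermediate-volume centres.
- Restate the precision that 270 evaluable patients give at those rates. Give the ICA–ECA power too: about 72–77% per cohort pair at the smallest gap implied with no overlap or independence.
- At the interim, do not read every cohort against a common 85%. Reconcile that benchmark and the 75% exclusion rule with the tabulated rates, and show the chance of exclusion at the ECA planning rate.

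The cost is rewording and a short calculation, and the stated ECA precision may become slightly less favourable. No added enrolment or data collection is needed.

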### Interventions

Patients will be recruited to one of four cohorts, depending on the surgeon’s experience: 1) Robotic right colectomy with ICA; 2) robotic right colectomy with ECA; 3) laparoscopic right colectomy with ICA; 4) laparoscopic right colectomy with ECA. For the ICA cohorts, Pfannenstiel incision will be the chosen wound for specimen extraction. If an operation cannot be completed using any of these minimally-invasive techniques, the patient will be considered a conversion to open surgery. Per protocol, conversion is defined as when anything apart of the anastomosis has to be done through the laparotomy. If the anastomosis is not completely performed in an intracorporeal approach during an Intracorporeal Anastomosis Case, the case is considered also converted.

MIRCAST Study is an observational study which has all the advantages and limitations of an observational study. One of the main limitations is that the surgical technique will not be standardized. Different factors (wound protectors, antibiotics, bowel prep…) might have an impact in the co-primary endpoint. As standardizing the technique is not an option in an observational study, all factors that might have an influence in the co-primary endpoint will be registered in the electronic Case Report Forms.

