Patients with missing data in planned surgical approach will be be excluded from the study. Patients with missing data in any end-point will be excluded from the analyses on that end-point, and patients with missing data in variables included in the propensity score will have their data imputed using multiple imputation procedures.

Three sensitivity analyses will be used for the primary end-points. The analysis will be repeated k times omitting a hospital each time (k = number of participant hospitals). In addition to intention-to-treat analysis, a sensitivity analysis will be conducted excluding patients with conversion. The analysis will be repeated stratifying by tertiles of the propensity score.

Stata/SE software will be used to perform the statistical analysis (versions 14–16 [forthcoming]).

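### The score called a propensity score is defined as a model of the outcome, not of cohort membership, so it can shrink technique effects and does not clearly serve the secondary endpoints

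*Protocol article*

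**What the plan says.** The Statistical analysis section defines the score in a single sentence, as a patient-level logit taken from the fit "of a logistic regression model in which the outcome is modeled with different potential confounding factors". The next sentence gives its use: "The propensity score will be added as a continuous variable to adjust the risk models". The sensitivity analyses in the same section use it again: "The analysis will be repeated stratifying by tertiles of the propensity score". The Sample size calculation section makes it the basis of between-cohort inference, which is to be done a posteriori "using a propensity score to account for confounding covariates".

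The exposure has four levels: "Patients will be recruited to one of four cohorts", assigned by surgeon experience and not at random. For the secondary endpoints the section names model types only: "GLM with identity link will be used for operative time, number of harvested lymph nodes and length of stay", logit-link models for the binary endpoints, and "Cox regression will be used for middle-term oncologic results". It does not say whether a score enters these models or which one. It refers to a separate SAP, which is not at hand.

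**The concern.** A propensity score is the probability of being in a treatment group given baseline covariates. Conditioning on it balances those covariates between groups, for any endpoint. A score that predicts the outcome from the covariates is a different tool. It summarises prognosis for one endpoint, and whether it behaves well depends on how treatment is handled when it is fitted.

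If it is fitted on all patients with technique left out, covariates that differ between cohorts act partly as stand-ins for technique. On the logit scale the score is then roughly βX + δ·e(X), where βX is the true prognostic part, δ the technique effect and e(X) the chance of being in the cohort given X. Adjusting for this score removes some of δ. Nothing is lost if δ = 0 or if e(X) does not vary with X.

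Two further consequences follow. A score built on wound infection and severe complications gives little weight to covariates that matter only for other endpoints. It also does not show whether the cohorts overlap or are balanced. The tertile analysis cannot expose any of this, because it stratifies on the same score.

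**Working it through.** The plan gives no figure to reproduce here. The check has two parts.

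**Reading the text.** The dependent variable in the defining sentence is the outcome and the predictors are potential confounders. Neither cohort nor technique is a dependent variable anywhere in the article. Technique is not listed as a predictor in the score model, so omitting it is the literal reading.

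**Simulation.** From the plan: success rate 85% (event rate about 15%), 300 patients per cohort (600 per pair), two-sided 0.05. Assumed, because the document gives no such figures:
- two cohorts and five standard-normal confounders, three of them prognostic for the primary endpoint (log OR 0.4 each);
- intercept −1.9, so risk at average covariates is 1/(1 + e^1.9) = 13%;
- true technique log OR of 0 or −0.70 (e^−0.70 = 0.50);
- confounder–technique log OR of 0.2, 0.4 or 0.7 per covariate (weak, moderate, strong).

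*True log OR −0.70, N = 20,000 (40 runs, to remove small-sample bias), mean estimate:*

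| Confounding | Crude | Outcome score, technique omitted | Outcome score, technique in model, covariate part only | Cohort-membership score |
|---|---|---|---|---|
| Weak | −0.445 | −0.682 | −0.698 | −0.683 |
| Moderate | −0.282 | −0.645 | −0.705 | −0.692 |
| Strong | −0.103 | −0.556 | −0.698 | −0.684 |

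Attenuation with the literal score:
- weak: 1 − 0.682/0.70 = 2.6% (OR 0.51);
- moderate: 1 − 0.645/0.70 = 7.9% (OR 0.52);
- strong: 1 − 0.556/0.70 = 20.6% (OR 0.57).

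The cohort-membership score itself sits 1% to 2% short of −0.70. The shortfall due to the literal score is therefore nil in the weak case (−0.682 against −0.683), 0.692 − 0.645 = 0.047 in the moderate case and 0.684 − 0.556 = 0.128 in the strong case.

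Power at N = 600 (600 runs), literal score against full covariate adjustment: 0.727 v 0.738, 0.650 v 0.688, 0.513 v 0.605.

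*No true effect, N = 600.* Crude log ORs are 0.228, 0.391 and 0.566. With the literal score they are 0.015, 0.005 and 0.010, with rejection rates of 0.057, 0.037 and 0.027.

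*A continuous secondary endpoint* (residual SD 1) with no true technique effect and three confounders, only one of them prognostic for the primary endpoint. N = 20,000, technique log OR −0.70 on the primary:

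| Confounding | Crude difference | Score built on primary outcome | Share of bias left |
|---|---|---|---|
| Weak | 0.173 | 0.132 | 76% |
| Moderate | 0.305 | 0.263 | 86% |
| Strong | 0.430 | 0.423 | 98% |

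A cohort-membership score, or a score built on that endpoint, leaves about 0.00 in each case.

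**The case against.** The strongest reply is that the harm is conditional.

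- **Technique may be in the score model.** The text does not state that it is omitted. If it is included and only the covariate part is used, the attenuation disappears. This stands, although omission is the more natural reading.
- **Strong confounding may not occur.** The Study setting section asks surgeons to keep to their technique on all consecutive eligible patients, which limits patient-by-patient selection. The same section lets surgeons enrol in any cohort for which they qualify, and case mix can differ between centres. No figure in the article supports the strong case, so 21% is the top of an assumed range and not an expected value.
- **The adjustment still works under the null.** A reader might infer that confounding of the primary endpoint goes uncontrolled or that false positives rise. The null results above contradict both for measured confounders.
- **Secondary endpoints.** A reader might infer that they are under-adjusted as planned. The article does not say that the primary-outcome score is reused, and endpoint-specific scores would avoid the problem. However, the only score defined is logistic, which does not suit operative time, node counts, length of stay or time-to-event endpoints.
- **Four cohorts.** A reader might infer that a binary score is wrong in any case. It is not: inference is pairwise, and a separate binary score for each pair is legitimate.
- **Balance.** Descriptive statistics by cohort can show imbalance. The limit is only that this score does not do so.

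The word outcome might have been used loosely for the dependent variable, meaning cohort. Nothing in the article supports that, and the sentence would still need correcting. Nor is this a detail left to the SAP: the article states a definition, and the definition is wrong. An SAP that follows it inherits the error, and one that models cohort membership contradicts it.

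**Conclusion.** The point holds as an error of definition. The planned confounding adjustment for the pairwise comparisons, and one of the three sensitivity analyses, rest on a prognostic score labelled as a propensity score.

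The consequences are possible, not certain. If technique is omitted from the score model and the cohorts differ on prognostic covariates, a true odds ratio of 0.50 is attenuated by about 3% to 21% on the log-odds scale over the assumed range, with no loss relative to a true propensity score at the weak end. If the primary-outcome score is reused for secondary endpoints, most of the bias from their own confounders can remain (76% to 98% in the example, where only one of three confounders was shared). These sizes depend on the assumed confounding strengths and covariate structure.

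**What to change.** Replace the defining sentence. Suggested content: *Planned cohort is modelled on pre-operative confounders, without any outcome, by multinomial logistic regression over the four cohorts or by a binary logistic model for each pairwise comparison. Overlap of the scores and standardized differences between cohorts are reported. The tertile sensitivity analysis uses this score.*

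For oncologic endpoints, add tumour stage as a separate prognostic covariate in the outcome model. Table 1 places pathology at the 30-day visit, so pathological stage is not a pre-operative variable and does not belong in the cohort model.

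Alternatively, keep the outcome-based approach under its right name. Call it a prognostic score, fit it with technique in the model, carry forward only the covariate part, and define a score of suitable form for each endpoint. The standard error should then allow for estimation of the score. In the simulation this version gave the same estimates as full covariate adjustment but rejected slightly more often under the null (0.067, 0.053, 0.065 against 0.060, 0.045, 0.038).

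Either way, state which score, if any, enters each secondary model. The cost is a change of wording in the protocol and SAP, best made before outcome data are analysed. A cohort-membership score may give slightly larger standard errors.
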